### Intervention {11a} {11b} {11c}

The intervention will consist of IPTp-SP with or without screen-and-treat using DP at the first ANC visit. Participants randomized to the IPTp-SP+ group who test positive by rapid diagnostic test (RDT) will be given a full treatment course of DP (D-ARTEPP® 40 mg/320 mg three tablets daily for 3 days; Guilin Pharmaceutical) under direct observation (DOT) by a study nurse (day 0) or community health worker (days 1–2). All other participants will be treated with SP at the first visit, including those in the IPTp-SP+ arm with a negative RDT result, and all participants in both groups will be given SP at all subsequent visits (day 35, day 63, then monthly until delivery) under DOT. IPTp-SP will be administered according to national guidelines (G-SCOPE® 1,500 mg sulfadoxine/75 mg pyrimethamine for one dose no fewer than 4 weeks between doses; Guilin Pharmaceutical). Participants will be observed for 1 h post-dose to monitor for vomiting or other adverse reactions. If vomiting occurs within 30 min, the full dose will be readministered. If vomiting occurs after 30 min, half of the total dose will be readministered. In the case of persistent vomiting, the participant will be withdrawn from the study and referred for alternative treatment.

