### Trial objectives {7} {12}

This research protocol is designed to assess the safety and efficacy of a revised IPTp schedule that incorporates a screen-and-treat strategy using RDT and DP at the first antenatal care visit (IPTp-SP+). The research objectives and corresponding endpoints are listed in Table 1.

**Table 1 Tab1:** Outcomes

Objectives	Outcomes/endpoints
Primary objectives	
To compare the effectiveness of IPTp-SP versus IPTp-SP+ for treating and preventing maternal *P. falciparum* infection To compare the safety and tolerability of IPTp-SP versus IPTp-SP+	• Relative hazard of *P. falciparum* infection diagnosed by PCR at day 42 after randomization (primary outcome) • Relative hazard of *P. falciparum* infection diagnosed by PCR or microscopy at days 14, 28, 35, 42, 63, delivery, and 1-month post-partum in infants • Proportion who experience at least one episode of *P. falciparum* infection by day 14, 28, 35, 42, or 63 • Proportion with treatment or prevention failure at day 42 stratified according to study drug (SP or DP) • Median time to first episode of MIP • Acute, chronic, and prior placental infection at delivery • Medication-related adverse events and serious adverse events until 1-year post-partum (primary outcome)
Secondary objectives	
To compare the effectiveness of IPTp-SP versus IPTp-SP+ for reducing complications of MIP	• Mean birth weight and prevalence of low birth weight (within 72 hours post-partum), neonatal mortality (within 28 days post-partum), congenital malaria diagnosed by PCR, placental malaria diagnosed by histopathology using placental biopsies, maternal anemia (hemoglobin changes at days 14, 28, 42 and 63), congenital anemia, Incidences of pregnancy losses, congenital *P. falciparum* infection
To compare selection for drug resistant parasites between infected individuals in the IPTp-SP and IPTp-SP+ treatment groups	• Relative allele frequencies of genotypic markers of drug resistance in malaria parasites
To measure piperaquine exposure and duration	• Terminal elimination half-life of piperaquine determined by noncompartmental analysis of drug concentrations at 0, 14, 28, 35 and 42 days

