### Safety assessments {22}

Drug safety will be monitored at every visit during the course of the study in compliance with International Conference on Harmonization Good Clinical Practice guidelines for adverse events (AEs) and serious adverse events (SAEs) [26]. All expected and unexpected AEs will be collected and reported in trial publications. SAEs will be reported to the sponsor and the ethics committee within 24 working hours of the study staff first becoming aware. Investigators will determine the relationship between safety signals and the study drugs and define outcomes, according to standard classifications [26].

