### Sample size calculation {14}

The sample size was determined based on available data and with the objective of achieving a detectable difference of a 50% reduction in the incidence of MIP. In 2019, Nchelenge District recorded 7791 live births (unpublished data). Prior studies in the same population found PCR prevalence of *P. falciparum* parasitemia to be 22–26% in pregnant women [14, 15]. A sample size of 324 pregnant women (*n*=162 per arm) will afford 80% power to detect a 50% difference of effect between study arms with a two-tailed alpha of 0.05. To allow for loss to follow-up of up to 20%, a total of 392 (*n*=196 per arm) will be recruited.

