### Participant retention and withdrawal {18b}

To facilitate retention in the study, participants will be issued study visit cards that include the dates of their follow-up visits. We will collect participants’ telephone numbers and physical addresses to allow the study team to contact participants in case of missed visits, advising them to report to the clinic for their scheduled visit within the window period of 3 days. Participants are allowed to leave the study at any time for any reason without any consequences. Participants will be withdrawn from the study only if they withdraw informed consent.

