### Statistical analysis {20a} {20b} {20c}

Longitudinal data will be displayed using the nonparametric Kaplan-Meier estimations of the survival function. The primary analysis will be comparison of the 42-day incidence of MIP using multivariate models to estimate the relative hazard between the IPTp-SP and IPTp-SP+ groups according to intention-to-treat (ITT). Testing for proportionality of hazards will be done using formal statistical testing with Schoenfeld residuals as well as visual inspection of the nonparametric survival estimates. For non-proportional hazards, an extended Cox model will be applied. To handle interval censoring due to participants who miss one or more follow-up visits, we will use parametric models for interval-censored survival-time data. The relative hazard will be estimated in parametric models accounting for recurrent events by using a robust variance estimator. For the primary safety analysis, we will compare the proportions of serious and non-serious AEs using logistic regression models and relative hazards of AEs using Cox regression methods as above. Secondary analyses of continuous outcomes (hemoglobin concentration, birthweight) will be examined in linear regression models and in logistic regression models for binary outcomes (prevalence of low birth weight, neonatal mortality, placental malaria, congenital malaria, maternal anemia, congenital anemia, drug resistance allele frequency). Prespecified subgroup analyses will be done according to the following strata: primigravidae, multigravidae, gestational age at enrollment, delivery before or after the day 63 visit, treatment dose on a mg/kg basis, positive *P. falciparum* PCR on enrollment, and presence or absence of quintuple and sextuple mutations. In a secondary analysis, we will compare the proportions of treatment failures and prevention failures according to the antimalarial drug given at the first encounter (SP or DP) in an on-treatment analysis using logistic regression. Treatment failures will be defined as recurrent infections that are determined by genotyping to be recrudescent parasites from the initial infection in participants who tested positive by PCR at the initial visit. Prevention failures will be defined as PCR-confirmed parasitemia in participants who initially tested negative by PCR at the first visit, or who tested positive by PCR at the first visit but who experienced reinfection with a new parasite as determined by genotyping. No interim analysis is planned. Every effort will be made to collect complete data for all participants and minimize missing data. Missing data will be handled using multiple imputation.

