## Trial status

This is protocol version 2.2 dated 28 October 2019. Recruitment began on 22 April 2019 and ended on 19 June 2020 with data collection still ongoing. This protocol was not submitted for publication during the active enrollment period due to delays caused by the coronavirus pandemic and medical emergency with prolonged recovery of one of our senior team members.

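### Two withdrawal rules conflict: persistent vomiting removes a woman from the study in one section, while another allows withdrawal only on loss of consent

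*Protocol article*

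**What the plan says.** The Intervention section of the protocol article covers re-dosing after vomiting within or after 30 minutes and then states: "In the case of persistent vomiting, the participant will be withdrawn from the study and referred for alternative treatment". The rule applies to every supervised dose, SP or DP, in both arms.

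The section Participant retention and withdrawal states: "Participants will be withdrawn from the study only if they withdraw informed consent".

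Three other sections determine what follows from the conflict:

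- Table 1 makes two outcomes primary: PCR-diagnosed infection at day 42, and medication-related and serious adverse events to one year post-partum.
- Statistical analysis makes the day-42 comparison intention-to-treat and adds: "Missing data will be handled using multiple imputation".
- Safety assessments states: "All expected and unexpected AEs will be collected and reported in trial publications".

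**The concern.** Both rules speak of withdrawal from the study, and persistent vomiting is not withdrawal of consent. The article has no rule that separates stopping study drug from stopping follow-up.

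If the Intervention rule is applied, the vomiting itself is still recorded, through the one-hour observation and the adverse event evaluations on days 0–2 and at later visits in Table 3. What is lost comes afterwards: the remaining dried-blood-spot PCR visits, the delivery and placental outcomes, and the infant visits at 1, 6, 9 and 12 months. The rule thus ends safety follow-up in women who have just reacted to study drug, although safety to one year is a primary outcome.

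The loss is also caused by treatment, and exposure to the rule differs between arms because only the IPTp-SP+ arm gives the three-day DP course. Neither censoring nor multiple imputation is sure to correct a loss of that kind.

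**Working it through.** **The two rules side by side.** The Intervention section makes persistent vomiting a ground for withdrawal. The retention section makes loss of consent the only ground. Any woman who vomits persistently and keeps her consent is withdrawn under the first rule and kept under the second.

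**What is lost if the Intervention rule prevails.**

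| Withdrawn after | Lost for the day-42 outcome | Also lost |
|---|---|---|
| Day 0, 1 or 2 dose | All post-baseline PCR | Delivery and infant outcomes |
| Day 35 dose | Day-42 PCR | Day-63 visit, delivery and infant outcomes |
| Day 63 or later dose | Nothing | Delivery and infant outcomes |

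Safety follow-up lost after a day-0 withdrawal, with enrolment at 16–26 weeks (Table 2) and delivery at an assumed 40 weeks:

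- enrolled at 26 weeks: (40 − 26) + 52 = 66 weeks
- enrolled at 16 weeks: (40 − 16) + 52 = 76 weeks

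**How many women.** The protocol gives no vomiting rate and no RDT positivity, so this is an illustration only.

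Inputs:

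- 196 women per arm (Sample size calculation).
- Dosing occasions before day 42 (Intervention): 2 for a woman given SP first (days 0 and 35); 4 for an RDT-positive woman in IPTp-SP+ (days 0, 1, 2 and 35).
- Fraction RDT-positive, f = 0.10–0.26. This is an assumption; the protocol's 22–26% is a PCR prevalence.
- Persistent vomiting per occasion, v = 0.2–1%, equal for both drugs. This is an assumption.

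Occasions:

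- Control: 196 × 2 = 392. (This equals the total number of women recruited only by coincidence.)
- IPTp-SP+: 196 × [2(1 − f) + 4f] = 196 × 2.20 = 431 at f = 0.10, and 196 × 2.52 = 494 at f = 0.26.
- Ratio to control: 1.10 to 1.26.

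Women withdrawn = occasions × v:

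| | v = 0.2%, f = 0.10 | v = 1%, f = 0.26 |
|---|---|---|
| Control | 0.8 | 3.9 |
| IPTp-SP+ | 0.9 | 4.9 |
| Total | 1.6 | 8.9 |
| Difference | 0.1 | 1.0 |

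The extra occasions all fall on the DP recipients, who number 196 × 0.10 ≈ 20 to 196 × 0.26 ≈ 51. These women also supply the piperaquine concentrations and the DP side of the failure analysis by drug.

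**Power.** The stated evaluable size is 162 per arm (324 in all). Taking 24% against 12% (24% is the midpoint of 22–26%, an assumption), two-sided 5% and 80% power:

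n = [1.960 × √(2 × 0.18 × 0.82) + 0.842 × √(0.24 × 0.76 + 0.12 × 0.88)]² / 0.12² ≈ 160 per arm, close to the stated 162.

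Recruitment allows 392 − 324 = 68 extra women, against the 2–9 above. If losses reached the full 20%, 196 × 0.80 = 156.8 per arm would remain, with power 74.9%, 79.3% and 83.1% at control rates of 22%, 24% and 26%. A further 2% withdrawn for vomiting (2% of 392 is about 8 women) lowers these to 73.8%, 78.2% and 82.2%, about one point each.

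**The case against.** The strongest reply is that no data need be lost. The retention section is the dedicated place for withdrawal and states a general rule with an explicit restriction. The vomiting clause sits in the dosing section, is tied to referral for other treatment, and could be read as stopping medication only. The intention-to-treat principle and the stated effort to collect complete data support that reading. It is right that the harm is conditional: if sites follow the retention section, follow-up continues. But the reading needs words that the vomiting clause does not contain. It says the woman leaves the study.

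It can also be said that the article is condensed, and that its version history mentions statements on analysis populations and non-adherence that are not reproduced. So the absence of a separating rule should carry little weight. That is fair, and the point does not depend on it: it rests on two sentences that are both printed and disagree.

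On size, both rates are assumed, and counting each DP day as carrying the same risk as a full SP dose is a simplification. A between-arm difference of about one woman will hardly move the day-42 hazard ratio. This stands.

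On imputation, the vomiting is recorded and so can enter the model. That helps only in part. If the rule is followed consistently, no woman with persistent vomiting has later outcomes observed, so the model must borrow from women who did not vomit persistently.

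Finally, little dosing remained to be changed. "Recruitment began on 22 April 2019 and ended on 19 June 2020 with data collection still ongoing". A woman enrolled on the last day at 16 weeks would reach 40 weeks 24 weeks later, on about 4 December 2020. Her infant's 12-month visit would fall about December 2021. This stands for dosing, but it leaves room to recover infant outcomes.

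**Conclusion.** The concern holds. The article gives two rules that cannot both be followed, and the one in the Intervention section, taken as written, ends follow-up because of a reaction to study drug. That affects the intention-to-treat day-42 outcome and the primary safety outcome to one year.

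The expected number is small: about 2–9 women by day 42 and a net arm difference of 0.1–1, on assumed vomiting and RDT-positivity rates. Power is not at stake. For each woman withdrawn on day 0 the loss is large: all post-baseline PCR and about 66–76 weeks of safety follow-up. Confidence is medium, because the article does not show which rule sites applied. The point should be corrected, but it does not threaten the trial's main conclusion.

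**What to change.** Reword the Intervention sentence so that persistent vomiting stops study drug only, with referral for alternative treatment. The woman and her infant stay in all scheduled follow-up unless consent is withdrawn, as the retention section already provides, and are analysed as randomised.

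Because recruitment has ended and first-visit dosing is over, two further steps matter more in practice:

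- For women already withdrawn under the vomiting rule, seek the remaining delivery and infant outcomes, with consent.
- In the participant flow, report the number withdrawn for vomiting by arm and by drug given, so that readers can judge the possible bias.

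The cost is a one-sentence clarification, a few extra follow-up visits and one line in the report. Day-42 PCR samples already missed cannot be recovered.

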### Clinical procedures {11d} {13} {15} {26a}

Study procedures are outlined in Table 3 and the flow of events is shown in Fig. 1. The informed consent will be administered by a study nurse in the local language (Bemba) and/or in English as preferred by the participant. Assent will be obtained from participants <18 years old, and informed consent will be obtained from those ≥18 or the legally authorized representative for minors. If the participant cannot provide a written signature, then a thumbprint will be obtained. After collection of demographic data, provision of informed consent, baseline medical and obstetric history, and physical examination by a study physician including eligibility assessment, participants will be randomized to either the IPTp-SP or IPTp-SP+ treatment groups. All participants will undergo hemoglobin measurement as part of the screening process. On enrollment, fingerstick blood will be drawn for preparation of dried blood spots (DBS) for subsequent molecular testing. In addition, participants randomized to the experimental group (IPTp-SP+) will undergo RDT.

**Table 3 Tab3:** Schedule of events

	Antenatal period *Study day*									Postpartum period *Study month*			
Event	0	1–2	14	28	35	42	63^a^	Unsch.	Birth	1	6	9	12
Informed consent/oral assent	•												
Medical history	•												
Physical examination, including height, weight, temperature	•		•	•	•	•	•	•	•				
Fetal viability	•		•	•	•	•	•	•	•				
Focused history and examination			•	•	•	•	•	•	•	•	•	•	•
Adverse event evaluation	•	•	•	•	•	•	•	•					
IPTp-SP^b^	•				•		•						
RDT^c^	•												
Treatment with DP^d^	•	•											
DBS for PCR, genotyping	•		•	•	•	•	•	•	•				
Malaria microscopy^e^			•	•	•	•	•	•	•				
Hemoglobin measurement	•		•	•		•	•		•	•			
Blood sample for PK^d^	•		•	•	•	•							
Delivery									•				
Placental biopsy, cord blood									•				
Infant assessment including history and exam, weight, heel stick									•	•	•	•	•

^a^Monthly visits continue until delivery

^b^Includes participants randomized to standard IPTp-SP, participants randomized to IPTp-SP+ who test negative at the first visit, and all participants in both groups at days 35, 63 and then monthly until delivery

^c^Limited to participants randomized to IPTp-SP+

^d^Limited to participants randomized to IPTp-SP+ who test positive by RDT at the first visit

^e^Only participants with signs or symptoms of malaria will undergo microscopy

*DBS* dried blood spot, *DP* dihydroartemisinin-piperaquine, *IPTp-SP* intermittent preventive treatment in pregnancy with sulfadoxine-pyrimethamine, *PCR* polymerase chain reaction, *PK* pharmacokinetics, *RDT* rapid diagnostic test for *P. falciparum* infection

**Fig. 1 Fig1:**
[figure not shown]
Study flow diagram. *ANC*, antenatal care. *DP*, dihydroartemisinin-piperaquine. *IPTp-SP,* intermittent preventive treatment in pregnancy with sulfadoxine-pyrimethamine with (+) or without screen-and-treat. *RDT*, rapid diagnostic test for *P. falciparum* infection

Treatment with either SP or DP will be administered as described above. Participants will return for follow-up on days 14, 28, 35, 42, and 63 and then monthly thereafter until delivery. They will be instructed to report to the clinic for any illness between scheduled visits.

At each scheduled or unscheduled visit, the study clinician will perform an interval history and physical examination, including an updated medication history. During the active follow-up period (up to day 63), DBS will be collected and hemoglobin will be measured. SP will be given on days 35 and 63. Additional doses of SP will be given during monthly visits until delivery with a minimum of 4 weeks between doses and laboratory samples (e.g., blood slide for microscopy, urinary tests, full blood count) will be collected if clinically indicated according to signs and symptoms. Antimalarials or antibiotics with antimalarial activity (e.g., systemic erythromycin, macrolide antibiotics, trimethoprim-sulfamethoxazole or other sulphonamides, tetracyclines, quinolones, clindamycin) will be prohibited during the active follow-up period.

Participants who present during the follow-up period with any signs or symptoms of malaria will undergo testing by thick smear, and DBS will be collected from those with positive microscopy. The signs and symptoms that we will consider indicative of possible clinical malaria include fever, chills, weakness, fatigue, myalgia, arthralgia, headache, anorexia, nausea, vomiting, abdominal pain, or diarrhea. All confirmed uncomplicated malaria cases will be treated with artemether-lumefantrine according to national guidelines (Coartem™ 20 mg/120 mg four tablets taken at 0, 8, 24, 36, 48, and 60 h). Participants who develop severe malaria defined according to WHO criteria will be referred to SPGH for inpatient management [20].

On the day of delivery, the participant and infant will be evaluated as soon as possible after delivery. The birthweight will be measured, and an assessment for congenital abnormalities will be done. Obstetric complications including but not limited to hemorrhage, premature rupture of membranes, cesarean section, and others will be captured as adverse events. Congenital abnormalities, if present, will also be recorded. Thick and thin peripheral blood films, DBS, and hemoglobin measurement will be done on both the participant and infant. In addition, cord blood, placental blood films for thick and thin smear microscopy, placental DBS, and placental biopsy for histopathological analysis will be collected.

Infants will be reassessed at 1, 6, 9, and 12 months postpartum for focused history and physical examination, including interval medication and hospitalization history, growth, and assessment of developmental milestones. At the first monthly visit, hemoglobin measurement and malaria parasitology by thick smear and PCR testing using DBS prepared from heel stick blood will be performed.

### Laboratory procedures {33}

#### Malaria microscopy

Thick blood smears will be stained with 3% Giemsa for 30 min and examined by trained microscopists. Parasite densities will be calculated by counting the number of asexual parasites per 200 leukocytes and the parasite density will be estimated assuming 8000 leukocytes per microliter. A slide will be determined negative after counting 2000 leukocytes. A thin blood smear will be made for species identification and quantification of high parasitemia (>16,000 parasites/μL). Non-falciparum species, gametocytes, and other malaria pigments will be reported but not quantified. Each slide will be read separately by two independent experienced microscopists who will remain masked to treatment assignment.

#### Point-of-care testing

Malaria point-of-care diagnostic testing will be done via *P. falciparum* HRP2 antigen-based RDT (SD BIOLINE, Abbott, IL, USA). Hemoglobin concentrations will be measured using a point-of-care Hb 201 Hemocue® Analyser (Angelholm, Sweden).

#### Placental histopathology

At the time of delivery, a 1-cm^3^ biopsy specimen will be obtained from the maternal-facing side of the placenta. Biopsy specimens will be preserved in 10% neutral buffered formalin and embedded in paraffin wax. Pending histological evaluation, tissue will be kept at 4°C. Paraffin sections 4 mm thick will be stained with hematoxylin and eosin stain. Placental biopsies will be classified according to the following definitions: acute infection (parasites present, malaria pigment absent), chronic infection (both parasites and malaria pigment present), past infection (parasites absent, malaria pigment present), or no infection (both parasites and malaria pigment absent) [21].

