### Study population {10} {15}

Pregnant women in the second and third trimesters attending routine ANC visits at the study health facilities will be systematically screened for potential enrollment. Inclusion and exclusion criteria are listed in Table 2. All volunteer pregnant women presenting to the ANC for the first time of their current pregnancy will be assessed for eligibility according to the following criteria: age ≥15 years, estimated gestational age 16–26 weeks, hemoglobin concentration ≥7 g/dL, ability to provide informed consent, residence in the study area with intention to deliver at the health center, no evidence of clinical malaria or other acute illness, and ability to tolerate oral medication. Women will be deemed ineligible for any of the following: infection with human immunodeficiency virus (HIV) or unknown HIV status, prior IPTp-SP or other antimalarial use or antimicrobials with antimalarial activity during the current pregnancy, intolerance to either of the study drugs, existing or prior obstetric complications, prior enrollment in the study or concurrent enrollment in another study, concurrent medications with potential for drug-drug interactions or potentiation of cardiac arrhythmia, presence of chronic illness or other factor deemed likely to influence the pregnancy outcome, or other reason which is judged by the investigator to render the individual unsuitable for study participation.

**Table 2 Tab2:** Inclusion and exclusion criteria

Inclusion criteria	
• Ability and willingness to provide informed consent^a^	
• Gestational age of 16 to 26 weeks at enrollment	
• Asymptomatic on presentation, with or without a positive RDT test result^b^	
• Age ≥15 years	
• Residence within the study catchment area and no intent to move out of the study catchment area before delivery or to deliver outside of the catchment area	
• Willingness to adhere to all study requirements including to deliver at the health facility	
• Ability to take oral medication	
Exclusion criteria	
• Infection with HIV at enrollment or unknown HIV status^c^	
• History of IPTp-SP or other antimalarial drug use during the current pregnancy	
• History of intolerance or allergic reaction to any of the study drugs	
• History of known pregnancy complications or bad obstetric history including pre-existing illness likely to cause complication of pregnancy such as repeated abortions, stillbirths or eclampsia	
• Hemoglobin concentration <7 g/dL	

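### Placental malaria is analysed as one binary outcome with no stated cut-point or baseline-infection adjustment; if past infection counts as positive, pre-randomisation pigment weakens the comparison.

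*Protocol article*

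**What the plan says.** All references are to the protocol article.

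- **Placental histopathology** sorts biopsies into four classes: acute, chronic, past and none. Past is "past infection (parasites absent, malaria pigment present"). Only one class is negative: "no infection (both parasites and malaria pigment absent").
- **Table 1** names placental outcomes twice. Under the primary objectives, but not marked as a primary outcome, it lists "Acute, chronic, and prior placental infection at delivery". Under the secondary objectives it lists "placental malaria diagnosed by histopathology using placental biopsies".
- **Statistical analysis** puts placental malaria among the outcomes for "logistic regression models for binary outcomes (prevalence of low birth weight, neonatal mortality, placental malaria, congenital malaria" and others. It names no covariate for this model and does not say which classes are positive. It does prespecify a subgroup by enrolment PCR, which the Limitations section repeats.
- **Study population** sets entry at "Gestational age of 16 to 26 weeks at enrollment", admits asymptomatic women whether or not an RDT is positive, and excludes prior antimalarial use in this pregnancy.
- **Sample size calculation** says that earlier studies in this population "found PCR prevalence of *P. falciparum* parasitemia to be 22–26% in pregnant women".
- **Table 3** schedules a day-0 dried blood spot for PCR in both arms.

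**The concern.** Pigment seen at delivery carries no date in this classification. A woman already infected at entry can be classed as past at delivery whichever arm she is in. If past counts as positive, two things follow.

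1. Infections that predate randomisation add positives to both arms, which pulls the ratio towards one.
2. A baseline infection that DP clears (past, if pigment remains) scores the same as one that persists under SP (chronic). The Discussion gives better clearance of early infections as the first justification for the strategy, so the binary outcome would be blind to the effect it should help to show.

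Preventing placental malaria is a stated secondary objective. The risk is that a real benefit reads as little or none.

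**Working it through.** **1. The plan's own figure.** Inputs from the sample size section: 22–26% prevalence, 50% reduction, two-sided 0.05, 80% power. At the 24% midpoint, with mean rate 0.18:

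n = [1.96·√(2·0.18·0.82) + 0.842·√(0.24·0.76 + 0.12·0.88)]² / 0.12² = 160 per arm.

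The plan states 162, where power is 80.6%. (22% vs 11% needs 178; 26% vs 13% needs 145.) No stated figure is disputed. This calculation concerns malaria infection; the protocol gives no rate for placental malaria.

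**2. Dilution if any infection is positive.** Assumptions, none from the documents: later placental infection is 24% vs 12%; baseline infection is 22–26%; a share s of baseline infections leaves pigment at delivery; 162 per arm are assessed. With f = baseline prevalence × s, arm risk = 1 − (1 − f)(1 − r), where r = 0.24 or 0.12.

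| s | f | Control | IPTp-SP+ | Risk ratio | Power |
|---|---|---|---|---|---|
| 0 | 0 | 24.0% | 12.0% | 0.50 | 81% |
| 25% | 0.055–0.065 | 28.2–28.9% | 16.8–17.7% | 0.60–0.61 | 67–69% |
| 50% | 0.11–0.13 | 32.4–33.9% | 21.7–23.4% | 0.67–0.69 | 55–58% |
| 100% | 0.22–0.26 | 40.7–43.8% | 31.4–34.9% | 0.77–0.80 | 37–42% |

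Example, f = 0.11: 1 − 0.89·0.76 = 0.324 and 1 − 0.89·0.88 = 0.217; ratio 0.67.

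If positive means parasites present (acute plus chronic), f drops out and the first row applies. This simple model treats every later infection as still active at delivery.

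**3. Does adjustment for day-0 PCR help?** Logistic regression was simulated at 24% baseline prevalence (1,500 runs, simulation error about 1.3 points).

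- *Same relative effect in all women.* Power rises from 56% to 63%, 46% to 62% and 42% to 65% at 50%, 75% and 90% persistence.
- *Effect only in baseline-positive women* (assumed 50% vs 25%, others 15.8% in both arms). This is closer to the design, because RDT-negative women in IPTp-SP+ receive the same SP as controls. Adjustment changes almost nothing: 10% to 12%, 6% to 6% and 6% to 5%.

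**4. Does the active-infection contrast help in that second case?** Control: 0.24·0.50 + 0.76·0.158 = 24.0%. IPTp-SP+: 0.24·0.25 + 0.76·0.158 = 18.0%. Any-infection rates at 50% persistence are 0.24·0.75 + 0.12 = 30.0% and 0.24·0.625 + 0.12 = 27.0%; at 90% they are 34.8% and 34.2%. In simulation, power is 5–8% for any infection and 25–28% for acute plus chronic. That is still low, but the difference between arms remains visible.

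**The case against.** **The cut-point is inferred.** No section says that past infection counts as positive. If positive means parasites present, both problems vanish, and a SAP could say so. This stands, and the point is conditional on it. However, the protocol already fixes the four classes, the binary form and the model; Table 1 treats prior infection as placental infection; and only one class is called no infection. Nothing rules out the reading that causes the trouble.

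**Much of the remedy is already there.** Table 1 keeps acute, chronic and prior infection apart, and a subgroup by enrolment PCR is prespecified. A reader might infer that the trial cannot credit DP for clearing baseline infections. The documents do not support that: clearance moves a woman from chronic to past, and the separate classes would show it. What remains is that the Statistical analysis section states no between-arm contrast for those classes. The PCR subgroup, if it uses the any-infection outcome, still scores cleared and persisting infections alike.

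**Past infection is not all unpreventable.** A reader might take the class to hold only infections that neither regimen could have prevented. It also holds infections acquired after randomisation and cleared before delivery, which are legitimate events. Dropping the class would lose them.

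**Randomisation balances earlier pigment in expectation.** This stands. The cost is attenuation and lost power; there is no push towards a false positive.

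**The power figures do not model this trial.** This largely stands. Pigment persistence has no source here, parasitaemia rates stand in for placental rates, and the gain from adjustment depends on where the effect lies.

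**Conclusion.** The point holds in a conditional form. The plan has one binary placental outcome with an unstated cut-point, no baseline-infection adjustment and no stated contrast that separates active from past infection. On the any-infection reading, pigment from before randomisation dilutes the comparison and clearance of baseline infection goes uncredited in that outcome.

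The direction is secure on that reading; the size is not. Under the assumptions shown, a true risk ratio of 0.50 would appear as 0.60–0.80 and power would fall from 81% to between 37% and 69%, depending on how much pigment persists. The gain from adjustment alone is real only if the effect is not confined to baseline-positive women. The acute-plus-chronic contrast helps in both cases examined. The endpoint is secondary, and the primary day-42 PCR comparison is untouched. It is worth correcting because the change costs so little.

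**What to change.** In the Statistical analysis section:

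1. State which histology classes make placental malaria positive.
2. Adjust the placental malaria logistic model for day-0 PCR status.
3. Prespecify a between-arm comparison of active placental infection (acute plus chronic).
4. Report past infection separately, by arm and day-0 PCR status.
5. Keep the any-infection outcome beside these.

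The cost is analysis wording only: the day-0 blood spots and the four histology classes are already in the schedule. The small downside is that the active-only contrast misses infections acquired and cleared after randomisation, which is why the any-infection outcome and the past-infection line should stay.
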